## Abstract

Controlling type 2 diabetes (T2DM) requires a comprehensive approach including patient education, self-monitoring of blood glucose, individualized behavioral strategies, and frequent contact with healthcare professionals (HCPs). We aimed to compare the efficacy of a personalized lifestyle intervention based on a mobile phone application with regular care in participants with T2DM. This is an ongoing randomized controlled open-label parallel-group trial with a target accrual of 282 participants, of which 181 have been enrolled to date. Participants are randomly assigned to one of three groups: (1) regular care; (2) mobile diabetes management; or (3) mobile diabetes management with HCP feedback. The mobile application is enabled to integrate with both electronic medical records (EMR) and a web-based diabetes management system for HCPs. It can send customized messages based on participants’ responses to lifestyle questionnaires administered at the baseline. The intervention period is 26 weeks followed by observation for 26 weeks. We evaluate the intervention’s features in order to assess its clinical utility and efficacy and compare outcomes with regular care considering relevant clinical factors, such as age, baseline HbA1c, etc. We expect our study to provide new evidence in support of customized mobile application tools for the management of T2DM.

## 1. Introduction

Diabetes mellitus is a major health concern affecting 463 million people worldwide [1]. Due to related complications and comorbidities, an estimated 4.2 million deaths were attributed to diabetes in 2019 [1,2]. Intensive glycemic control can reduce morbidity and mortality by decreasing micro- and macrovascular complications [3]. However, to achieve glycemic goals, in addition to medical treatment, self-management strategies, including diet, exercise, and self-monitoring of blood glucose (SMBG), are essential. Its complex nature challenges patients and providers to properly manage diabetes, with only 25.1% of patients meeting the glycated hemoglobin (HbA1c) target of <6.5% and 52.6% meeting the HbA1c target of <7.0% in Korea [4]. Furthermore, only 8.4% of patients with diabetes met combined glycemic, lipid, and blood pressure goals [4]. In the United States, 37.0% and 7.3% of patients, respectively, met the HbA1c target of <7.0% and combined glycemic, lipid, and blood pressure goals [5]. Taken together, these data indicate how difficult it is to achieve target glycemic goals despite remarkable advances in anti-diabetes medications.

In response to this concern, mobile applications have recently emerged as a promising technology to enable effective self-management of diabetes. These tools can aid patients with diabetes by increasing awareness of and modifying behavior through reminder and/or feedback [6]. Such applications allow remote assessment and prompt intervention by healthcare professionals (HCPs) between visits, especially in urgent situations, such as hypoglycemia or severe hyperglycemia [7]. Mobile applications have been reported as superior to interventions such as text messaging, mobile device use, or conventional self-management. Several meta-analyses have shown that use of mobile applications can reduce HbA1c levels by 0.5%, with an even greater reduction when combined with HCP feedback [7,8,9].

Notwithstanding, several limitations have been observed in previous studies of mobile applications. Interventions were heterogeneous, not individualized, and not compared with simple interventions such as regular calls or automated alert messages [10,11]. Clinical effects varied among interventions and were generally modest [10]. Although the important role of HCPs is well understood, it has not been evaluated simultaneously with mobile applications and, while several studies evaluated cost effectiveness, the results were inconclusive [12,13].

To address these weaknesses, we designed a diabetes management system using an electronic medical record (EMR)-integrated mobile application to support type 2 diabetes (T2DM) management (Figure 1). The purpose of this study is to evaluate the utility, clinical efficacy, and cost effectiveness of a personalized diabetes management system (with and without HCP feedback) using an EMR-integrated mobile application in participants with T2DM compared with regular care. 

## 2. Materials and Methods

### 2.1. Study Design

This study is an open-label parallel-group three-arm randomized controlled trial conducted at two clinical study sites in Seoul, Korea: St. Vincent’s Hospital and St. Mary’s Hospital. The trial was registered at https://cris.nih.go.kr/cris/index.jsp (accessed on 1 January 2020), Clinical Research Information Service (CRIS), Republic of Korea (No. KCT0004128). Eligible participants are randomly assigned to one of the following three groups: (1) regular care; (2) mobile diabetes management; or (3) mobile diabetes management with personalized HCP feedback (Figure 1 and Figure 2). The participants are seen every 12 weeks ± 2 weeks. This trial is composed of two phases: a 26-week intervention period and a subsequent 26-week observation period. During the intervention period, the participants are managed according to the relevant protocols. In the subsequent observation period, the participants are managed the same as during intervention but without HCP feedback in Group 3 (Figure 2). This trial is ongoing; the first participant was enrolled in August 2019, and the final participant will be observed through December 2021.

### 2.2. Intervention

Regardless of the assigned group, all the participants are provided a glucometer (CareSens^®^N IoT, i-SENS, Inc., Seoul, Korea) during the intervention period along with diabetes education including SMBG, diet, and exercise.

The participants in Group 1 (the control group) receive regular care according to the Korean Diabetes Association standards [14]. They are instructed to conduct SMBG four times/day (before the morning meal and 2 h after every meal) and record it. Providers monitor SMBG at every visit and provide regular care (Table 1).

In Groups 2 and 3 (intervention groups), the diabetes management system (iCareD application, Medical Excellence Inc., Seoul, Korea) is used in addition to regular care (Table 1). The instruction for SMBG is the same for all the groups; however, as glucometers transmit data wirelessly through mobile communication technology (long-term evolution), the participants in Groups 2 and 3 can track their SMBG data using the application without manual recording. Further, they can visually track the glycemic status as the glucose level is differentiated by color in the application (Table 2). For example, grey signifies potential hypoglycemia; green indicates a glycemic level within the target range; and red indicates a very high glucose level (Table 2, Figure 3A). The participants are also instructed to upload diet photos through the application. Physical activity is tracked using the Google Fit^®^ mobile application [15]. These data are uploaded to the web-based diabetes management system which is integrated to the EMR system for HCP use. At every visit, providers individualize the intervention based on the data. The participants in Groups 2 and 3 also receive messages about diabetes management through the application three times/week (two standardized messages for diabetes management and lifestyle modification and one customized message depending on the lifestyle questionnaire completed at the baseline). The messages consist of information on general diabetes management, diet, physical activity, and encouragement for self-care (Supplementary Table S1). The messages were developed based on the standard diabetes care and were verified by an independent endocrinologist, nurse, nutritionist, and exercise therapist. The participants in Groups 2 and 3 also receive a monthly report generated from their personal data (glucose, blood pressure, physical activity, and diet) (Figure 3B).

In Group 3, providers remotely monitor the participants’ data between visits and provide additional feedback every two weeks. The messages generally reflect three areas: glycemic status, diet, and physical activity. The participants in Group 3 may directly message providers and receive immediate feedback as needed. Individual feedback between visits will be provided only during the intervention period. There is no difference in intervention between Groups 2 and 3 during the observation period.

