### 2.4. Primary and Secondary Outcomes

The primary outcome is the change in HbA1c (%) from the baseline to week 26. The secondary outcome is the change in HbA1c (%) and fasting glucose (mg/dL) from week 26 to week 52. Other secondary outcomes include lifestyle changes based on physical activity and diet records; cardiometabolic risk factors (body weight, blood pressure, lipid profile); quality of life using Euro-QOL (EQ-5D-5L); participant satisfaction and adherence; number of unscheduled hospital visits due to hypoglycemia or hyperglycemia; number of hypoglycemia and hyperglycemia episodes; changes in the homeostasis model assessment for insulin resistance and β cell function (HOMA-IR and HOMA-β, respectively); and cost effectiveness.

Exploratory outcomes are the change in diabetes medication; frequency of SMBG; BMI; and albuminuria. Study results will be shared with participants and the larger medical research community through presentation at conferences and publication in peer-reviewed journals.

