Hypoglycemic events, including hospitalization or emergency room visits, are evaluated at every visit. Hypoglycemia is defined as blood glucose level < 70 mg/dL or when participants experience symptoms consistent with hypoglycemia, such as sweating, anxiety, or shakiness, and relief of those symptoms occurs following ingestion of glucose [22,23]. Diabetes management strategies, such as SMBG frequency, physical activity, and diet, are obtained at every visit. Quality of life is assessed using the Korean version of the Euro-QOL (EQ-5D-5L) instrument at the baseline and once every 26 weeks [24,25]. The EQ-5D-5L comprises five dimensions (mobility, self-care, usual activities, pain/discomfort, and anxiety/depression) rated on a scale of five (none, slight, moderate, severe, and extreme). User satisfaction with the mobile application will be surveyed in Groups 2 and 3 at the end of the study. Adherence will be assessed by evaluating the scheduled visits, SMBG frequency, maintenance of physical activity and diet record, and achievement of the HbA1c goal. Any adverse events occurring during the trial will be monitored until resolution and reported as required.

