**Figure 3 ijerph-18-05300-f003:**
[figure not shown]
Examples of visual information of glycemic status (**a**) and a monthly report (**b**) on a web-based diabetes management system integrated with a mobile application.

**Table 1 ijerph-18-05300-t001:** Comparison of intervention protocols for each group.

Components	Control	Intervention	
	Group 1	Group 2	Group 3
Education	Comprehensive management of diabetes, including self-care	Comprehensive management of diabetes, including self-care	Comprehensive management of diabetes, including self-care
Instruction	Conduct and record SMBG four times/day	Conduct and record SMBG four times/day, upload diet photos	Conduct and record SMBG four times/day, upload diet photos
Monitoring	SMBG and lifestyle * questionnaire, laboratory data	SMBG and lifestyle * log in the web-based system, individualized monthly reports about comprehensive management, laboratory data	SMBG and lifestyle * log in the web-based system, individualized monthly reports about comprehensive management, laboratory data
Intervention	Regular care only	Regular care with mobile diabetes management	Regular care with mobile diabetes management
Feedback from HCPs	During the visits (every 13 weeks)	During the visits (every 13 weeks)	During the visits (every 13 weeks) and between the visits (every two weeks) through the mobile application
Immediate intervention between visits	Not possible	Not possible	Possible
Interactive patient–physician communication between visits	No	No	Yes

* Diet and physical activities. HCP: healthcare professional; SMBG: self-monitoring blood glucose.

**Table 2 ijerph-18-05300-t002:** Visual information of operational glycemic status on the mobile application in the intervention group.

Level	Assessment	Color Code	Glucose Level (mg/dL)				
			Preprandial	Postprandial	Bedtime	Dawn	Other
1	Severe hypoglycemia	Black ■	<50	<50	<50	<50	<50
2	Hypoglycemia	Dark grey ■	50–69	50–69	50–69	50–69	50–69
3	Potential hypoglycemia	Grey ■	70–79	70–89	70–89	70–79	70–79
4	Within the target	Green ■	80–130	90–180	90–139	80–130	80–130
5	Above the target	Yellow ■	131–179	181–249	140–249	131–179	131–179
6	High	Orange ■	180–249	250–349	250–349	180–249	180–249
7	Very high	Red ■	≥250	≥350	≥350	≥250	≥250

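### Self-recorded readings in control against transmitted readings in the app arms put glucose episodes, SMBG frequency and lifestyle outcomes at risk of differential ascertainment, and adherence is defined partly by reaching the HbA1c goal

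*Protocol article*

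**What the plan says.** **How readings are captured.** Section 2.2 says of Group 1: "They are instructed to conduct SMBG four times/day (before the morning meal and 2 h after every meal) and record it". For the app arms, the meters transmit by mobile network and "the participants in Groups 2 and 3 can track their SMBG data using the application without manual recording". The testing schedule itself does not differ: "The instruction for SMBG is the same for all the groups". Nor does the device: "all the participants are provided a glucometer (CareSens^®^N IoT, i-SENS, Inc., Seoul, Korea) during the intervention period".

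**How lifestyle is captured.** The monitoring row of Table 1 gives Group 1 "SMBG and lifestyle * questionnaire, laboratory data" and Groups 2 and 3 "SMBG and lifestyle * log in the web-based system". In the app arms, section 2.2 tracks activity with Google Fit and asks participants to upload diet photos.

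**Which outcomes depend on this.** Section 2.4 lists as secondary outcomes the number of hypo- and hyperglycemia episodes, adherence, and "lifestyle changes based on physical activity and diet records". SMBG frequency is exploratory. Section 2.5 counts as hypoglycemia any glucose below 70 mg/dL, or typical symptoms relieved by glucose. Section 2.8 compares the number of hypoglycemic events between groups with a chi-squared or Fisher's exact test.

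**How adherence is assessed.** Section 2.5 names scheduled visits, SMBG frequency, and then "maintenance of physical activity and diet record, and achievement of the HbA1c goal".

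**The concern.** An outcome compared between randomized arms should be collected in the same way in each arm. Here the route by which a reading or a lifestyle entry reaches the study is part of what is randomized. A low value that a Group 1 participant does not write down may never be counted; the same value in Group 2 or 3 is transmitted. Group 3 also has remote review every two weeks and direct messaging, which give a further chance of detection.

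The directions differ by outcome. Under-recording in control would make the app arms look worse on glucose episodes and better on SMBG frequency and on any adherence measure that uses it.

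Adherence has two further problems that need no assumption about under-recording. It includes reaching the HbA1c goal, which overlaps the primary outcome, so an arm with more effective treatment would tend to look more adherent on that component. It also includes a diet record, for which control has no stated counterpart to the photo uploads.

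**Working it through.** The plan gives no figure to reproduce on this point. The check sets out the stated source of each outcome by arm, then shows scale under labelled assumptions.

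**1. Stated sources, side by side**

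| Item | Group 1 | Groups 2 and 3 | Described without arm restriction |
|---|---|---|---|
| SMBG readings | Recorded by the participant (2.2) | Transmitted by the meter (2.2) | Same meter and same testing instruction (2.2) |
| Activity and diet | Questionnaire (Table 1) | Web-based log; Google Fit and uploaded photos (Table 1, 2.2) | K-GPAQ; lifestyle questionnaire at baseline, weeks 26 and 52 (2.5) |
| Hypoglycemia | Depends on readings for values below 70 mg/dL | Same definition, transmitted readings | Evaluated at every visit, symptoms included (2.5) |
| Diet record in adherence | No upload instructed (Table 1) | Photo upload instructed (Table 1) | None stated |
| HbA1c goal in adherence | Laboratory | Laboratory | Same source, but overlaps the efficacy outcome |

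The article does not say which of these sources feeds each between-group comparison.

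**2. Episode rates**

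With equal true rates, the observed app-to-control rate ratio equals the capture fraction in the app arm divided by that in control. The capture fractions are assumptions; none is in the article.

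- Complete app capture, 20% unrecorded in control: 1/(1 − 0.20) = 1.25.
- Complete app capture, 40% unrecorded in control: 1/(1 − 0.40) = 1.67.
- App capture of 98%, control 90%, 80%, 70% or 60%: 0.98/0.90 = 1.09, 0.98/0.80 = 1.22, 0.98/0.70 = 1.40, 0.98/0.60 = 1.63.

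**3. The planned chi-squared comparison**

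This test suits the proportion of participants with an event. Take 94 per group (section 2.6), an assumed true proportion of 30% in both arms, and capture of an affected participant of 98% in one app arm. The chance of a two-sided p < 0.05 showing more events in the app arm is approximately Φ{[(p₂ − p₁) − 1.96 × SE₀]/SE₁}, with SE₀ from the pooled proportion and SE₁ from the separate ones.

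Worked case, control capture 60%: p₁ = 0.30 × 0.60 = 0.180, p₂ = 0.30 × 0.98 = 0.294, pooled 0.237, SE₀ = 0.0620, SE₁ = 0.0615, so Φ(−0.12) = 0.45.

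| Capture in control | Observed, control | Observed, app arm | Chance of a spurious result against the app |
|---|---|---|---|
| 90% | 0.270 | 0.294 | 5.5% |
| 80% | 0.240 | 0.294 | 13% |
| 70% | 0.210 | 0.294 | 26% |
| 60% | 0.180 | 0.294 | 45% |

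With equal capture the figure in that direction is 2.5%. For true proportions from 20% to 40%, and the same control capture fractions, the range is about 5% to 61%.

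**4. SMBG frequency**

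Four tests a day is 4 × 7 = 28 a week. If everyone tests as instructed, the apparent gap is 28 × (0.98 − control capture): 2.2, 5.0, 7.8 and 10.6 tests a week at control capture of 90%, 80%, 70% and 60%, with no real difference.

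**The case against.** The best reply is that section 2.2 and Table 1 describe the intervention, not outcome measurement. Table 1 compares intervention protocols, and its monitoring row may mean only what providers look at during care. All arms have the same networked meter, so Group 1 readings may already be retrieved from it. A journal article may leave the data source per outcome to the full protocol. Section 2.5 describes the K-GPAQ, a lifestyle questionnaire and enquiry about hypoglycemia at each visit without restricting them to any arm. Symptomatic episodes need no written reading, and unscheduled hospital visits do not depend on the log.

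Much of this stands. A reader might infer that the comparisons are biased as a matter of fact, that control uses a paper log, or that everything in the app arms is automatic. The article supports none of these: it never states the source used for each comparison, it says only that Group 1 records its readings, and diet photos are uploaded by the participant. The rate ratios are also not predictions for the planned test. A participant with several low readings is still counted if one is recorded: with two low readings and independent omission, the chance of missing both is 0.20² = 4% to 0.40² = 16%, not 20% to 40%.

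Three things remain. The arm-dependent capture is stated, not merely left open. Section 2.4 ties the lifestyle outcome to records, although common questionnaires exist. And section 2.5 names HbA1c goal attainment as adherence. It is true that no composite adherence score is given, and that no analysis is planned that uses adherence to explain the HbA1c effect. So the claim that a better arm must score as more adherent overall goes too far; the overlap on that component does not.

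**Conclusion.** The point holds as a risk, not as demonstrated bias. SMBG frequency, value-based hypo- and hyperglycemia episodes and record-based lifestyle outcomes are open to differential ascertainment, and the adherence definition mixes in the efficacy result and an item instructed only in the app arms. The size of any bias is unknown. The illustrative rate ratio of 1.25 to 1.67 rests on two assumptions, 20% to 40% of control low readings unrecorded and complete app capture, and on no recovery of missed readings at visits.

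No stronger reading is warranted. The primary outcome is a laboratory measure and is untouched; the affected outcomes are secondary or exploratory. The change should still be made, because it is specific and cheap and most of what it needs is already described for all arms.

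**What to change.** - **SMBG frequency and threshold-based episodes:** take them in all three arms from the readings stored in or transmitted by the common glucometer, downloaded at existing visits. This assumes that Group 1 readings are retrievable. Where they are not, including for participants already enrolled, label the comparison descriptive. Section 2.2 states meter provision for the intervention period only, so state the source after week 26 as well.
- **Lifestyle outcome:** base it on the K-GPAQ and on the lifestyle questionnaire at baseline, week 26 and week 52, confirmed as given to all arms. Keep tracker and photo data for description within Groups 2 and 3.
- **Adherence:** remove HbA1c goal attainment and app-only items from the definition. Report HbA1c goal attainment as an efficacy outcome; section 2.8 already has a model for it.

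The cost is a small amount of staff time for meter downloads in Group 1 and revised outcome wording. No extra visit or laboratory test is needed.

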### 2.3. Eligibility

Eligible participants must meet all the inclusion criteria: (1) patients with T2DM who need SBMG and who underwent self-management training; (2) age of 19–74 years; (3) HbA1c ≥ 7.5%; (4) body mass index (BMI, calculated as kg/m^2^) ≥ 18.5 kg/m^2^; (5) ability to use a smartphone; and (6) written informed consent.

Exclusion criteria are: (1) insulin pump use; (2) estimated glomerular filtration rate < 30 mL/min/1.73 m^2^; (3) heart failure (New York Heart Association class III–IV); (4) diagnosis of cancer within five years; (5) recipient of an organ transplant or need in long-term immunosuppressant therapy; (6) difficulty in exercise and physical activity due to spinal disease (intervertebral disc prolapse, spinal stenosis, etc.), joint disease, or major surgery at the time of screening; (7) plan to receive surgery that could limit physical activity during the study period; (8) pregnant or breastfeeding; (9) plan to become pregnant or disagreement with using adequate contraception during the study period; (10) participation in another clinical trial (other than an observational one) within 90 days; and (11) inappropriate candidate as judged by an investigator.

### 2.4. Primary and Secondary Outcomes

The primary outcome is the change in HbA1c (%) from the baseline to week 26. The secondary outcome is the change in HbA1c (%) and fasting glucose (mg/dL) from week 26 to week 52. Other secondary outcomes include lifestyle changes based on physical activity and diet records; cardiometabolic risk factors (body weight, blood pressure, lipid profile); quality of life using Euro-QOL (EQ-5D-5L); participant satisfaction and adherence; number of unscheduled hospital visits due to hypoglycemia or hyperglycemia; number of hypoglycemia and hyperglycemia episodes; changes in the homeostasis model assessment for insulin resistance and β cell function (HOMA-IR and HOMA-β, respectively); and cost effectiveness.

Exploratory outcomes are the change in diabetes medication; frequency of SMBG; BMI; and albuminuria. Study results will be shared with participants and the larger medical research community through presentation at conferences and publication in peer-reviewed journals.

